### Ground truth diagnosis

Patients will be classified into whether they have benign or malignant nodules as follows:

Benign-nodule patients:By resolution or stability of all qualifying incidental pulmonary nodules as determined from volumetry-based measurement on imaging follow-up over 12 months.By histopathology from biopsy or surgery of all qualifying incidental pulmonary nodules (within 12 months of baseline CT scan).Malignant-nodule patients:By histopathology from biopsy or surgery (within 12 months of baseline CT scan) of at least one qualifying incidental pulmonary nodule.Probable benign-nodule patients:By resolution, stability or shrinkage of qualifying incidental pulmonary nodules that are not in ground-truth outcomes #1 or #2 above as determined from volumetry-based measurement on imaging follow-up conducted between 3 and 12 months after the baseline CT scan.By resolution, stability or shrinkage of qualifying incidental pulmonary nodules that are not in ground-truth outcomes 1 or 2 above as determined from diameter-based measurement on imaging follow-up conducted 12 months after the baseline CT scan (supplemented with a volume-based measurement of the nodule that will be performed for research purposes).Probable malignant-nodule patients:By clinical diagnosis of lung cancer, in whom a biopsy or resection is not possible, based on high clinical probability and who are registered at a lung cancer MDT/and/or receive non-surgical treatment (stereotactic ablative radiotherapy (SABR)/radiotherapy/microwave ablation).

Volumetry-based measurement of nodule stability—and hence a benign diagnosis—will be satisfied if the lung nodule volume on the follow-up CT scan was <125% of the lung nodule volume on the baseline CT scan.

If the standard care at a particular site does not incorporate volumetry-based measurements, the volumetric measurement will be applied as part of the research study to the relevant follow-up CT scans.

Any lung nodule patients who do not fall into either of the two ground-truth outcomes 1 or 2 above will be considered to have an indeterminate diagnosis at the time of analysis and will be analysed with and without the inclusion of the ground-truth outcomes in 3 and 4.

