### Outcome measures

The outcome measures for the primary and secondary objectives are outlined in table 1.

**Table 1 T1:** Study objectives and outcome measures

Objective	Outcome measure
Primary: Determine the potential effect of the LCP on discharge	The measured difference between standard care and the three LCP-based options described under AI model for: No and percentage of cancer patients discharged (straight after assessment of the baseline scan). No and percentage of benign-nodule patients discharged (straight after assessment of the baseline scan).
Secondary: Determine the potential effect of the LCP on possible adherence to clinical guidelines	The measured difference between standard care and the three LCP-based options described under AI model: No and percentage of patients for whom a validated risk model (Brock or LCP) is used to guide the next clinical management step (ie, counting the instances where Brock is not used or where LCP is not possible to compute, or it is ignored).
Secondary: Determine the potential effect of the LCP on overall clinical management, as well as scan and procedure utilisation	No and percentage of cancer patients for whom there would have been a change in clinical management according to each of the three LCP-based options described under AI model compared with actual care (correctly for more aggressive management and incorrectly for less aggressive management). No and percentage of benign-nodule patients for whom there would have been a change in clinical management according to each of the three LCP-based options described under AI model compared with actual care (incorrectly by more aggressive management and correctly for less aggressive management). The measured difference between standard care and the three LCP-based options described under AI model for: No and percentage of CT scans and PET/CT scans performed on benign-nodule patients. No and percentage of non-surgical biopsies performed on benign-nodule patients. No and percentage of surgical excisions on benign-nodule patients.

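### A benign non-surgical biopsy makes a patient definitely benign even if the nodule later grows or an MDT later diagnoses lung cancer without tissue, and no planned analysis tests this

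*Protocol article*

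**What the plan says.** The Ground truth diagnosis section of the protocol article sorts patients into four outcomes: benign (1), malignant (2), probable benign (3) and probable malignant (4).

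- Outcome 1 has two routes, each sufficient. The imaging route is "By resolution or stability of all qualifying incidental pulmonary nodules as determined from volumetry-based measurement on imaging follow-up over 12 months". The tissue route is "By histopathology from biopsy or surgery of all qualifying incidental pulmonary nodules (within 12 months of baseline CT scan".
- Outcome 2 needs malignant tissue: "By histopathology from biopsy or surgery (within 12 months of baseline CT scan) of at least one qualifying incidental pulmonary nodule".
- Outcome 4 is reached "By clinical diagnosis of lung cancer, in whom a biopsy or resection is not possible, based on high clinical probability", with lung cancer MDT registration and/or non-surgical treatment.
- Stability, for the imaging route, means that the "lung nodule volume on the follow-up CT scan was <125% of the lung nodule volume on the baseline CT scan".
- The section closes with a residual rule, whose sentence labels the remaining patients as indeterminate: "Any lung nodule patients who do not fall into either of the two ground-truth outcomes 1 or 2 above will be considered to have an". The analysis of that remainder follows in the same sentence: they "will be analysed with and without the inclusion of the ground-truth outcomes in 3 and 4".

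The labels then define the denominators in Table 1 (Outcome measures). Both primary measures count discharges by label. Secondary measures include "No and percentage of non-surgical biopsies performed on benign-nodule patients", changes in management scored as correct or incorrect according to the label, and cancers by stage.

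**The concern.** An excision examines the whole nodule; a non-surgical biopsy examines part of it and can miss a cancer. The tissue route does not separate the two, and the 125% volume limit is attached only to the imaging route. A patient can therefore be definitely benign on an early biopsy although later scans, which the Data collection section says are sent to the software throughout follow-up, show growth that the imaging route would not accept as stable.

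This also sits oddly with the section's own grading of evidence. Volumetric stability on a scan between 3 and 12 months earns only the probable-benign label, while a benign biopsy soon after baseline earns the definite one whatever happens next.

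The label decides the sign of an LCP downgrade. Discharging a cancer is an LCP error; discharging a benign nodule is an LCP success. A cancer labelled benign turns the first into the second.

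**Working it through.** **Step 1. Run cases through the rule as written.**

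| Patient | Outcome 1 by tissue | Outcome 2 | Result |
|---|---|---|---|
| Benign excision of all qualifying nodules | met | no | definite benign; no concern |
| Two qualifying nodules, only one biopsied (benign) | not met | no | tissue route does not apply |
| Benign biopsy of all nodules, then malignant tissue within 12 months | benign result superseded | met | malignant; not part of the leak |
| Benign biopsy of all nodules, then volume at or above 125%, no further tissue | met | no | **definite benign** |
| Benign biopsy of all nodules, then lung cancer MDT diagnosis without malignant tissue | met | no | **definite benign** |

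The last two rows are the leak. The with/without analysis varies only outcomes 3 and 4, so these patients sit in outcome 1 in every stated analysis.

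**Step 2. Check the plan's figures that supply the discordance rate.** The Sample size section assumes that, among cancers, 0.4% are kept by Brock and discharged by LCP, and 2.6% the reverse. With n = [1.96·√p + z·√(p − d²)]²/d², where p is the sum of the two rates, d their difference and z the normal quantile for the stated power:

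- 0.4% against 2.6%, 90% power: 648 (stated 659).
- 1.0% against 2.3%, 90% power: 2048 (stated 2000).
- 13.5% against 17.0%, 80% power: 1952, or 2009 with continuity correction (stated 2026).

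The figures are reproduced closely enough that 0.4% can be used as the plan's own rate. They do not themselves bear on the classification rule.

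**Step 3. Number mislabelled (assumptions only).** The article gives no cancer prevalence, biopsy rate or biopsy false-negative rate.

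Mislabelled = cancers × share biopsied × false-negative share × share with no later malignant tissue.

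- Low: 100 × 0.4 × 0.05 × 0.5 = 1
- Middle: 200 × 0.6 × 0.10 × 0.5 = 6
- High: 300 × 0.6 × 0.15 × 0.5 = 13.5
- Much wider inputs (prevalence 5–20%, biopsied 30–80%, false negative 5–20%, uncorrected 25–100%): 2000 × 0.05 × 0.3 × 0.05 × 0.25 = 0.4 to 2000 × 0.20 × 0.8 × 0.20 × 1 = 64. The upper end is 64/(1600 + 64) = 3.8% of the benign group.

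**Step 4. Shift in the primary cancer comparison.** Biopsied patients were, with few exceptions, not discharged by standard care at baseline. So the only discordant cell the error can reach is the one where LCP discharges and standard care keeps. Expected number moved = mislabelled × 0.004:

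- 6 × 0.004 = 0.024
- 13.5 × 0.004 = 0.054
- 64 × 0.004 = 0.26

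To expect one moved patient, the LCP-only discharge rate among mislabelled cancers would have to be 1/6 = 17%, 1/13.5 = 7.4% or 1/64 = 1.6% respectively, all well above 0.4%.

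**The case against.** The strongest reply has four parts.

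- *The primary result is hardly touched.* This stands. With 100 to 300 cancers, the cell counting against LCP holds only 0.4 to 1.2 expected patients (0.4% × 100 to 300). A reader might infer that even one moved patient would distort it. But a mislabelled cancer must also be one that LCP alone would discharge, and Step 4 puts the expected number far below one. The 0.4% rate may not hold in the biopsied subset, but nothing in the article suggests a higher one.
- *Letting benign tissue stand where imaging is inconclusive is an ordinary choice, and the two routes are alternatives.* Also fair: failing the 125% limit does not make a nodule malignant, so this is not a contradiction. What remains is that contrary evidence in hand is given no weight.
- *The article condenses a fuller protocol.* How non-diagnostic samples are handled may be set out there, and that is not held against the plan. But the four-outcome rule is stated in detail, including which patients the with/without analysis covers.
- *The benign-biopsy outcome is a difference between strategies.* True: where both would lead to biopsy, a mislabelled cancer adds to both counts and cancels. It moves the difference only where they diverge, although the counts and percentages reported for each change in any case.

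A reader might also infer that a biopsy-negative patient later treated as lung cancer meets outcomes 1 and 4 together, with the closing sentence giving outcome 1 precedence. The text does not support that: outcome 4 is limited to patients who cannot be biopsied or resected, and the closing sentence only defines who is indeterminate. On either reading, nothing takes the patient out of outcome 1.

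**Conclusion.** The point holds in a narrow form. The rule keeps in the definite-benign class those patients whose benign non-surgical biopsy is later contradicted by growth or by an MDT diagnosis without malignant tissue, and no stated analysis tests the effect. It would be too strong to say that any benign biopsy suffices, since all qualifying nodules must be sampled, or that all false-negative biopsies stay in the benign group, since malignant tissue within 12 months meets outcome 2.

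The size cannot be derived from the article. Under the assumptions above, 1 to 13.5 patients are mislabelled (0.4 to 64 at wide extremes). The expected shift in the primary cancer comparison is about 0.02 to 0.05 of a patient for the middle and high cases and 0.26 at the extreme. Any shift would favour LCP, given that biopsied patients were kept by standard care. The more likely consequence is wrong labels in the secondary outcomes: a step-down scored as correct when it was not, indicated biopsies of cancers counted as biopsies of benign nodules, and cancers missing from the stage distribution.

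**What to change.** Change the research classification only:

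1. Keep benign surgical excision of all qualifying nodules as definite benign.
2. State that a benign non-surgical biopsy does not count as definite benign when follow-up already collected shows volume at or above 125% of baseline, or when a lung cancer MDT diagnosis follows. Move such patients to indeterminate or probable malignant, and word outcome 4 so that it is clear whether a patient with an earlier benign biopsy can enter it.
3. Add a sensitivity analysis in which patients who are benign by non-surgical biopsy alone, without imaging stability, move to probable benign.

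The cost is a few lines of wording and one further analysis, using tissue results, scans and final diagnoses that the Data collection section already plans to record. The downside is that a few patients leave the definite-benign group, some of them truly benign. Demanding confirmatory imaging for every non-specific biopsy in the main analysis would go too far: the Ethics and dissemination section plans no additional scans, so truly benign patients without a later scan would become indeterminate.

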### Outcome measures

The outcome measures for the primary and secondary objectives are outlined in table 1.

**Table 1 T1:** Study objectives and outcome measures

Objective	Outcome measure
Primary: Determine the potential effect of the LCP on discharge	The measured difference between standard care and the three LCP-based options described under AI model for: No and percentage of cancer patients discharged (straight after assessment of the baseline scan). No and percentage of benign-nodule patients discharged (straight after assessment of the baseline scan).
Secondary: Determine the potential effect of the LCP on possible adherence to clinical guidelines	The measured difference between standard care and the three LCP-based options described under AI model: No and percentage of patients for whom a validated risk model (Brock or LCP) is used to guide the next clinical management step (ie, counting the instances where Brock is not used or where LCP is not possible to compute, or it is ignored).
Secondary: Determine the potential effect of the LCP on overall clinical management, as well as scan and procedure utilisation	No and percentage of cancer patients for whom there would have been a change in clinical management according to each of the three LCP-based options described under AI model compared with actual care (correctly for more aggressive management and incorrectly for less aggressive management). No and percentage of benign-nodule patients for whom there would have been a change in clinical management according to each of the three LCP-based options described under AI model compared with actual care (incorrectly by more aggressive management and correctly for less aggressive management). The measured difference between standard care and the three LCP-based options described under AI model for: No and percentage of CT scans and PET/CT scans performed on benign-nodule patients. No and percentage of non-surgical biopsies performed on benign-nodule patients. No and percentage of surgical excisions on benign-nodule patients.
Secondary: Determine the potential effect of LCP-guided care vs standard care on patient outcomes	The measured difference between standard care and the three LCP-based options described under AI model for: No and percentage of thoracic, respiratory or vascular events related to biopsies or surgical excisions for lung nodules or suspected lung cancer occurring within 30 days of the procedure on benign-nodule patients. No and percentage of lung cancers stratified by stage. Time in days between nodule detection and lung cancer diagnosis.
Secondary: Determine the potential health-economic effect of LCP-guided care versus standard care	The measured difference between standard care and the three LCP-based options described under AI model for: The composite standardised GBP costs of all healthcare-related activity for lung nodules or suspected lung cancer. Health-related quality of life (using EQ-5D-5L to generate QALYs). Estimate cost-effectiveness (Incremental costs per QALY gained).

AI, artificial intelligence; LCP, lung cancer prediction; MDT, multi-disciplinary team; PET, positron emission tomography; QALY, quality-adjusted life year.

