## Abstract

**Introduction:**

In a small percentage of patients, pulmonary nodules found on CT scans are early lung cancers. Lung cancer detected at an early stage has a much better prognosis. The British Thoracic Society guideline on managing pulmonary nodules recommends using multivariable malignancy risk prediction models to assist in management. While these guidelines seem to be effective in clinical practice, recent data suggest that artificial intelligence (AI)-based malignant-nodule prediction solutions might outperform existing models.

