Optellum has developed and extensively validated an AI-based computer-aided diagnostic (CADx) tool for lung cancer prediction (LCP) in pulmonary nodules, which has UK Conformity Assessed marking under UK medical device regulations. The AI model underpinning the LCP is a convolutional neural network (CNN), referred to hereafter as the ‘LCP-CNN’. LCP-CNN was derived and internally validated using data from diverse populations from the USA and UK. The model was then externally validated in two independent cohorts of patients with incidentally detected pulmonary nodules, amounting to over 1500 patients in aggregate.^7 8^ The LCP-CNN demonstrated greater accuracy in these studies than the Brock and Mayo malignancy risk models (used in managing incidentally detected nodules in the UK and USA, respectively). The product is provided within the ‘Virtual Nodule Clinic’ (VNC), a software device used in the tracking, assessment and characterisation of incidentally detected pulmonary nodules.

The study aims to assess this new AI tool in a prospective real-world setting in the UK. This will be done by calculating malignancy risk using LCP and measuring how management would differ if it was governed by the risk provided. The aim is to provide evidence as to whether LCP should be the new standard of care in pulmonary nodule management.

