### Data collection

Study teams at the 12 NHS Trusts from which patients will be recruited will identify eligible patients and obtain informed consent. Consent will be obtained verbally (for patients who would not normally come on-site as part of standard care) or via written consent. Consent will be sought to analyse standard-care CT scans, associated clinical meta-data collection and the health economics assessment.

Once a patient has given consent and enrolled into the study, their baseline CT scan will be sent to VNC. Authorised research staff will then log into VNC, select the nodules of interest and record the LCP score for that nodule. The local standard nodule service decision-makers will provide a standard-care decision for eligible, consented patients via their usual nodule management pathway. The standard-care decision for eligible consented patients will then be recorded in an electronic case report form (eCRF) without knowing the LCP score.

To assess LCP under scenario #1 as described under AI model, the clinical team will thereafter be given the LCP score and relevant patient data in the nodule MDT or as part of a separate research meeting. At this point, the clinical team should remain blinded to the outcome of any actual-care investigation (eg, positron emission tomography (PET)/CT scan, biopsy). Their decision on the next management step, had they been guided by the LCP score, will then be recorded in the eCRF. The clinical team will have the option to modify management at this point. Any modification of management will be recorded in the eCRF.

Subsequent follow-up images for each patient will be sent to the VNC over the course of their nodule follow-up, and the final nodule diagnosis will be recorded. Since standard patient care can sometimes deviate from BTS guidelines, all participating sites will also collect information on patient and nodule characteristics necessary to follow the BTS guidelines. In this way, AI-guided management can be compared with BTS-compliant management. Other data points necessary to evaluate service utilisation (eg, additional scans, biopsies and treatments for lung nodules or lung cancers) will also be recorded in the eCRF.

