### Statistical analysis

#### Sample size

For calculations relating to the primary objectives of a measured difference between standard care and LCP for:

Number and percentage of cancer patients discharged: results from thresholds defined for discharge in a previous study are used.^7^ Based on previous data within the cancer group, assuming for the discordant pairs that the Brock model threshold (representing the standard of care) identified 0.4% of cancers for which the LCP threshold would have recommended discharge, and the LCP threshold correctly identified 2.6% of cancers for which the Brock model threshold would have recommended discharge, then using McNemar’s test with 90% power and a significance level of 0.05, 659 participants would be needed. However, with a sample size of 2000, there is 90% power to detect a difference between the methods if the percentages were as small as 1.0% and 2.3%, respectively.Number and percentage of benign-nodule patients discharged: again, results from thresholds defined for discharge in a previous study are used.^7^ Based on previous data within the benign group, assuming for the discordant pairs that 17.0% of benign nodules are recommended for discharge by the LCP threshold but not by the Brock model threshold. In comparison, 13.5% are recommended for discharge by the Brock model threshold but not by the LCP threshold; there is 80% power to detect a significant difference between the two tests with 2026 individuals using McNemar’s test. This equates to an OR of 1.26

Sample size calculations were performed using R statistical software (V.4.1.2; R Foundation for Statistical Computing, Vienna, Austria).

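### The guideline-adherence outcome in Table 1 counts whether Brock or LCP guided the next step, not whether that step agrees with the guideline, and so credits use of the device under test as adherence.

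*Protocol article*

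**What the plan says.** In the protocol article, Outcome measures, Table 1, one secondary objective reads "Determine the potential effect of the LCP on possible adherence to clinical guidelines". Its only measure, compared between standard care and the three LCP options, is "No and percentage of patients for whom a validated risk model (Brock or LCP) is used to guide the next clinical management step". The row explains what is tallied against this: "counting the instances where Brock is not used or where LCP is not possible to compute, or it is ignored".

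Three other places bear on it:

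- The abstract says the BTS guideline "recommends using multivariable malignancy risk prediction models to assist in management". The Introduction identifies Brock as the model used for incidental nodules in the UK. It also gives the study's aim as evidence on whether LCP should become standard of care.
- The AI model section lists three LCP options. In the first and third a physician decides with LCP information. In the second the LCP-CNN threshold alone decides on discharge.
- Data collection states the reason for gathering guideline inputs at every site: "Since standard patient care can sometimes deviate from BTS guidelines". It then states their purpose: "In this way, AI-guided management can be compared with BTS-compliant management".

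**The concern.** Adherence is a property of the decision: does the step taken match the step the guideline leads to? The row records a property of the process: did a risk model guide the step? These differ whenever a model guides a decision that is not the guideline's decision. Because LCP is accepted on the same footing as Brock, replacing the model used in UK practice with the investigational one counts as full adherence by definition.

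At stake is a reported gain in guideline adherence for LCP that reflects how often Brock goes unused in routine care, and says nothing about whether LCP-based decisions lie closer to or further from the guideline pathway. A reader or commissioner would probably take the label at face value.

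**Working it through.** The plan states no figure for this outcome, so the check has two parts: what the definition can respond to, and what scale of disagreement the plan itself assumes.

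**1. What the definition responds to.** Let *b* be the share of patients in whom Brock is not used in standard care, *u* the share in whom LCP cannot be computed, and *i* the share in whom a physician ignores a computable LCP. Reading the row literally:

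- Standard care: 100% − *b*
- Option 2 (threshold alone): 100% − *u*, since no physician is there to ignore the result
- Options 1 and 3 (physician-guided): 100% − *u* − *i*

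The contrast of option 2 with standard care is therefore (100% − *u*) − (100% − *b*) = *b* − *u*. No term depends on whether the decision agrees with the guideline. If every LCP threshold decision were reversed, the option 2 result would not change. Eligibility (Box 1) requires a CT series that meets the software's requirements, so *u* should be small.

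**2. Whether another row fills the gap.** The management-change rows use actual care as comparator and class changes as correct or incorrect by cancer or benign status. The remaining rows contrast the LCP options with standard care. Data collection itself treats standard care and BTS-compliant care as different things. No row has BTS-compliant management as its comparator.

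**3. Scale from the plan's own planning rates.** The Sample size section assumes that "17.0% of benign nodules are recommended for discharge by the LCP threshold but not by the Brock model threshold", with 13.5% in the other direction. For cancers it assumes 0.4% (LCP discharges, Brock does not) and 2.6% (the reverse).

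To confirm that these rates are read as intended: the odds ratio 17.0/13.5 = 1.26 matches the plan. With *p* the total discordance and *d* the difference, N = (1.96√*p* + z√(*p* − *d*²))² / *d*² gives:

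- Cancers (*p* = 0.030, *d* = 0.022, 90% power): 648, against 659 stated.
- Benign (*p* = 0.305, *d* = 0.035, 80% power): 1952, or 1981 with continuity correction, against 2026 stated.

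These are close enough to treat the rates as paired discordances. Then, for the threshold rule of option 2:

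- Benign: 17.0% + 13.5% = 30.5% discordant, so 69.5% agree.
- Cancers: 0.4% + 2.6% = 3.0% discordant, so 97.0% agree.

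The article gives no cancer prevalence. Assuming 5% to 20%, with every patient classed as cancer or benign:

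- 5%: 0.05 × 3.0% + 0.95 × 30.5% = 29.1%, about 582 of 2000.
- 20%: 0.20 × 3.0% + 0.80 × 30.5% = 25.0%, or 500 of 2000.

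Under the row as written, all of these option 2 decisions count as adherent.

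**The case against.** The strongest defence is that the guideline, as the article describes it, recommends using risk models, so counting model use measures a real element of adherence. The objective is also hedged with the word possible. This stands: the count is a legitimate process indicator and worth keeping. It does not make one element stand for the whole, and it does not explain why the device under test should qualify alongside Brock.

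The row also asks for more than a tool being consulted. It requires that the model guide the step, and it treats an ignored LCP as a failure. So it would be wrong to infer that merely computing a score counts, or that the measure can never fall. It falls if LCP is ignored or cannot be computed more often than Brock goes unused. What it cannot register is a model-guided step that departs from the guideline.

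A departure from BTS may be clinically correct, and the primary outcomes and management-change rows judge LCP decisions against diagnosis. That is true, and it is a reason to read agreement with BTS alongside those rows. It does not give the adherence objective a measure of its own.

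Finally, a journal article condenses the full protocol, and the BTS comparison may be specified there. The point does not rest on that omission: Table 1 states the adherence measure explicitly, and the stated measure does not match its objective.

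**Conclusion.** The mismatch holds. It follows from the text of Table 1 and needs no numerical assumption. It concerns one secondary outcome.

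The figures are illustrative only. A reader might infer from them that 30.5% of benign patients under LCP would be managed against the guideline, or that true adherence would be 69.5%. The documents do not support that. The rates compare LCP with a Brock discharge threshold taken from an earlier study. The article nowhere says that this threshold reproduces the BTS pathway, which by its own account also involves volumetry. The 500 to 582 patients further depend on the assumed prevalence, and they apply to option 2 only; nothing comparable is given for the physician-guided options. They show that the disagreement passing unrecorded could be substantial, not how large non-adherence would be.

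**What to change.** 1. Rename the existing count as use of a validated risk model and keep it as a descriptive outcome. Report Brock use and LCP use separately.
2. Add a paired secondary outcome: the number and percentage of patients whose recorded next step agrees with the BTS-compliant step, for standard care and for each LCP option. Derive the BTS-compliant step for each patient from the patient and nodule characteristics that Data collection says every site records. Fix the derivation rule before the LCP decisions are analysed. For option 2, which yields only discharge or not, define agreement on that binary decision.
3. State that this outcome is to be read with the correct and incorrect management-change rows, so that disagreement with BTS is not taken as error in itself.

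The cost is a change to one Table 1 row, one added row and some derivation programming, with no new data. The LCP adherence figure is likely to be less favourable than one near 100%.
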